### Qualitative Analysis

For the analysis and interpretation of the exit focus groups/interviews, we will use a qualitative descriptive methodology.^
12
^ Thematic analysis will be performed with the assistance of NVIVO. Thematic codes will be categorized and analyzed by 2 independent researchers using summative content analysis, incorporating both inductive and deductive approaches in the analysis.^
13
^

### Economic Assessment

We will use event rates and direct costs derived from the trial to re-calibrate our previously published Markov cost-effectiveness model in determining the cost utility of this intervention.^
14
^

### Sex and Gender Differences

We will collect information on both sex and gender at enrollment. We will perform a prespecified subgroup analysis given known differences in CKD progression by sex. We will also examine intervention uptake and adherence by gender in a sensitivity analysis, and the primary and secondary outcomes will be adjusted for gender if there are baseline imbalances between arms.

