### Sample Size Considerations

Based on systematic reviews of the published literature, we estimate a 39% reduction in the hazard of an outcome event (ie, hazard ratio [HR] = 0.61 for intervention).^6,7^ Further assuming an event rate in the usual care group of 11.4% per month,^
7
^ an expected median follow-up of 12 months per patient, a censoring rate of 3% per month, patient attrition of 10%, 2-ided alpha = 0.05, and beta = 0.10 (90% power), we will require 340 patients total (170 per arm), 68 patients/site.

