### Baseline Assessment

Baseline assessment will take place within 14 days of enrollment either virtually or in-person. During the baseline visit, the research coordinator will provide general instruction on how to complete the UK Kidney PREM and the KDQOL-SF via a virtual link. Baseline data collected will include sex, gender, race, age, eGFR, kidney failure risk equation (KFRE) score, patient-reported outcome measures (PROMs) (measured by KDQOL-SF questionnaire) and patient-reported experience measures (PREMs). Demographic characteristics, eGFR, and KFRE will be collected from patient charts/electronic medical record (EMR) and entered into REDCap; KDQOL-SF and PREM questionnaires will be completed by patients via REDCap.

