### Secondary Outcomes and Sensitivity Analyses

The same Kaplan-Meier survival curve approach will be used for the secondary outcomes of all-cause mortality, ED visits, hospitalization, and acute inpatient dialysis initiation. Change in overall KDQOL, UK Kidney PREM, and SUS scores will be assessed with a 2-sided t-test or Wilcoxon Rank Sum test as distributionally appropriate and interpreted relative to their minimal important differences. Sensitivity analyses will include (1) negative binomial regression and mixed linear models to account for repeated events; (2) multivariate Cox regression to adjust for any potential imbalances in prognostic covariates; and (3) an Andersen-Gill model to adjust for repeated events in the context of a time-to-event analysis.^
11
^ All outcomes will be assessed at a 2-sided alpha = 0.05. Subgroup analyses will be prespecified and limited to (1) eGFR greater or less than 10 mL/min, (2) sex and gender (described below), and (3) diabetes. A per-protocol analysis will be performed specifically and only to estimate the potential impact of patient non-adherence.

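### The primary test is fixed as unadjusted, yet gender adjustment of the primary outcome is made to depend on observed baseline imbalance; adjustment should be prespecified on prognostic grounds

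*Protocol article*

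**What the plan says.** Three places in the protocol article bear on covariate adjustment.

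- **Primary Analysis** compares the arms by intention to treat, using Kaplan-Meier curves and a log-rank test. It names no covariates. The abstract adds Cox models, described as univariate.
- **Secondary Outcomes and Sensitivity Analyses** lists, as its second sensitivity analysis, "multivariate Cox regression to adjust for any potential imbalances in prognostic covariates".
- **Sex and Gender Differences** says that "the primary and secondary outcomes will be adjusted for gender if there are baseline imbalances between arms".

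Two other sections matter for the remedy. Randomization is stratified by site. Under Baseline Assessment, "Baseline data collected will include sex, gender, race, age, eGFR, kidney failure risk equation (KFRE) score", so several candidate covariates are already in hand.

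**The concern.** With 1:1 central randomization, any baseline difference between arms is chance. Its observed size is a poor guide to whether a covariate belongs in the model. The sound reason to adjust is that the covariate predicts the outcome, and that can be judged before any data are seen.

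The gender sentence does the reverse for the primary outcome itself. The model is settled after the arms have been compared at baseline, and the text does not say whether the adjusted result replaces the log-rank result or accompanies it. Two versions of the primary result then exist, and a reader of the final report could not tell which one the plan had committed to. Meanwhile the covariates more likely to add precision are confined to a sensitivity model, again on the ground of imbalance.

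**Working it through.** **1. The passages side by side.** Primary Analysis gives one unadjusted test. Sex and Gender Differences gives the same outcome an adjusted analysis if a condition is met. The two agree only when the condition is not met. The sensitivity Cox model carries no trigger; it is planned in any case, with imbalance as its stated purpose. The data-dependent rule is therefore explicit for gender only.

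**2. The planned sample size.** The inputs from Sample Size Considerations are "hazard ratio [HR] = 0.61 for intervention", "an event rate in the usual care group of 11.4% per month", "an expected median follow-up of 12 months per patient", "a censoring rate of 3% per month", attrition of 10%, and "2-ided alpha = 0.05, and beta = 0.10 (90% power". I read the monthly rates as hazards and follow-up as a fixed 12 months.

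- Events (Schoenfeld): 4(1.960 + 1.282)² / (ln 0.61)² is just over 172, so 173.
- Event probability: λ/(λ+c) × [1 − exp(−12(λ+c))], with c = 0.03. Control (λ = 0.114) gives 0.651. VIEWER (λ = 0.61 × 0.114 = 0.0695) gives 0.487. The mean is 0.569.
- Patients: 173/0.569 rounds up to 305, and 305/0.90 = 339, against 340 stated.
- In reverse: 340 × 0.90 = 306 evaluable, 306 × 0.569 = 174 events, and power is 90.3%.

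Freedman's formula (180 events) with the rates read as monthly probabilities gives 342, also close. Mixing the two readings gives 328 or 353. The stated figure is sound for an unadjusted comparison.

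**3. What prespecified adjustment would add.** The document gives no prognostic strength, so a range is assumed. The simulation used 306 patients, the plan's rates, HR 0.61 as the covariate-conditional effect, and 3,000 trials per row:

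| Log-hazard SD of prognostic score | Log-rank power | Cox, always adjusted | Gain (points) |
|---|---|---|---|
| 0 | 89.3% | 89.5% | 0.2 |
| 0.3 | 86.7% | 88.8% | 2.1 |
| 0.5 | 83.2% | 88.7% | 5.5 |
| 0.8 | 70.6% | 84.8% | 14.2 |

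A separate simulation gave 89% against 91%, 85% against 89%, and 75% against 90% at SD 0.3, 0.5 and 0.8, with type I error near 5%. The absolute levels depend on calibration: at SD 0.8 the adjusted power is 84.0% with the mean control hazard fixed at 11.4% per month and 89.6% with the median fixed there. The gains are similar across runs.

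**4. The gender trigger itself.** The simulation took 46% female from the pilot described in the Discussion and an assumed gender log-hazard ratio of 0.2 (0.2 and 0.5 under the null).

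- Power: adjusting for gender alone changed it by less than 0.5 point.
- How often the trigger fires: with 306 patients the standardized difference has SD √(4/306) = 0.114. A cut-off of 0.1 is 0.87 SDs, exceeded by chance in about 38% of trials (38 to 41% simulated). A p<0.05 rule fires in about 5%.
- Type I error (5,000 null trials, Monte Carlo error about 0.3 point): 4.8 to 5.4% when the rule is applied mechanically, and 5.7 to 5.9% if whichever version is significant is reported.

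**The case against.** An unadjusted log-rank test is a valid primary analysis, and the sample size was computed for it. Covariate names and the definition of imbalance are commonly left to a statistical analysis plan, which is not shown here. For gender, the effect on power and error rate is slight. All of this stands. It does not remove the conflict between the two sections, nor the fact that the article states a data-dependent rule for the primary outcome.

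The covariates on hand may also be weaker than hoped. Eligibility (eGFR below 15, kidney failure risk above 40%) narrows the range of both measures. The risk equation predicts dialysis, which the primary analysis treats as censoring. The Discussion supports age, frailty and comorbidity as risk factors only in general terms. The upper end of the assumed range should be read with that in mind.

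A reader might infer more than the document supports:

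- *The trial falls short of 90% power.* It does not. The low log-rank figures arise from reading 0.61 as conditional. The average unadjusted HR is then about 0.64 at SD 0.5 and 0.67 at SD 0.8, a smaller effect than planned. The document takes 0.61 from systematic reviews and does not call it conditional.
- *Adjusting only when imbalanced recovers almost nothing.* That depends on the threshold and, for a strong score, on extending the gender rule to it. With |z|>1.96, power moved only from 85.5% to 85.9% (always adjusted: 90.9%) at SD 0.5. With a standardized difference above 0.1 it moved from 84.0% to 86.6% (always adjusted: 89.8%), which is 2.6/5.8, or about 45% of the gain.
- *Type I error rises to 7 or 8%.* That needs a strong score and deliberate reporting of the better of two models. Nothing in the document says this will be done.
- *Diabetes, a planned subgroup, will not be collected.* The baseline list is not stated to be exhaustive, and the article is condensed.

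**Conclusion.** The point holds in a limited form. The article gives the primary outcome an unadjusted test in one section and a conditionally adjusted analysis in another, with chance imbalance as the condition. That is a poor basis for adjustment and leaves the primary result open to a choice after the data are seen.

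For gender the numerical consequence is negligible. The larger matter is the precision forgone by keeping prognostic covariates out of the main estimate: about 0 to 6 points of power for a log-hazard SD up to 0.5, and about 15 points at 0.8. Those figures rest on assumed SDs and a conditional HR of 0.61, and they measure a gain over the unadjusted test. The change is worth making before unblinding, but the planned analysis is not invalid without it.

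**What to change.** - In Sex and Gender Differences, delete the condition on baseline imbalance. In the sensitivity analyses, delete imbalance as the reason for the multivariable Cox model.
- Prespecify a short set of baseline covariates already collected, for example age, sex or gender, and eGFR or the kidney failure risk score. Stratify by site, as the randomization does. Use this set whatever balance is observed.
- State which single analysis is primary, and show the unadjusted log-rank test and hazard ratio beside the adjusted result.

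The cost is protocol and analysis-plan wording, with no change to the 340 patients and no new data for the covariates named above. The drawback is that the adjusted hazard ratio is conditional on the covariates and will generally differ from the unadjusted one, which is why both should be shown.

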## Discussion

We designed a pragmatic clinical trial to investigate the impact of incorporating a virtual monitoring platform (VIEWER) into standard care for high-risk CKD patients. Our hypothesis is that the addition of VIEWER to usual care will result in a decrease in the risk of an ED visit or hospitalization compared with usual care alone.

Patients with advanced CKD face a vulnerable period when transitioning to dialysis which is reflected in high rates of ED visits before dialysis initiation.^
4
^ In a population-level retrospective cohort study in Manitoba, Canada, Komenda et al^
4
^ found that in a 7-day period before dialysis initiation, new dialysis patients were 9-fold more likely than prevalent dialysis patients, and 20-fold more likely than the general population to visit the ED. Vulnerability during this time is partly attributable to risk inherent in advanced CKD population such as age, frailty, and multiple comorbidities.^
4
^ Precipitating causes of ED visits often include fluid overload, hyperkalemia, bacteremia, and accelerated decline in kidney function.^
4
^ These precipitating events may be detectable by preceding changes in BP or weight and decreases in oxygen saturation and physical activity.^15
[Bibr bibr16-20543581251359736][Bibr bibr17-20543581251359736]-18^ Monitoring of these variables in advanced HF appears to improve patient outcome in health failure populations.^
6
^ Whether a similar strategy can prevent unplanned ED visits or hospitalizations in an advanced CKD population is unknown.

Uminski et al^
6
^ conducted a systematic review and meta-analysis evaluating the effects of post-discharge virtual wards on hospital readmissions compared to usual care. They found that when implemented for HF patients, multidisciplinary virtual monitoring (of weight, vital signs, and symptoms) can lower the risk of all-cause mortality and heart-failure-related hospital readmissions.^
6
^ In addition, Bamforth et al^
19
^ examined post-discharge interventions and their impact on reducing the likelihood of death and hospital readmissions in patients with HF, chronic obstructive pulmonary disease (COPD), and CKD. The authors found that post-discharge interventions decreased mortality and hospital admissions in HF and in COPD patients, but there was a gap in the research on the impact of these programs in patients with CKD.^
19
^ Both advanced CKD and HF share a significant number of similarities and exhibit symptoms which can be identified early and managed remotely, making virtual monitoring a promising preventative tool.^
6
^ As such, virtual monitoring in advanced CKD patients has the potential to improve health outcomes with a monitoring program that is specifically tailored to CKD.

The VIEWER is a disease-specific intervention which is looking at monitoring parameters relevant to the care of CKD patients who are approaching kidney failure and need to start dialysis. The VIEWER was created by a team of nephrology clinicians, data scientists, patient partners, and information technology collaborators. Significant effort went into making this platform accessible and easy to use.

The VIEWER provides daily data on BP, weight, blood oxygen saturation levels (SpO_2_), and physical activity levels. We pilot tested VIEWER in 36 CKD patients (80% with diabetes, average age 74, 46% female) to assess usability, acceptability, and adherence, and gather patient feedback.^
20
^ Results showed high usability (90/100 on SUS scale) and acceptable adherence with daily self-assessments (78%) (18).^
20
^ Even though adherence decreased at 3 months, >80% of participants continued to use the kit at least twice weekly even at 3 months.^
20
^ In total, 70% of participants asked if they could keep using the kits after the study, suggesting high acceptability.^
20
^

The VIEWER, a tablet-based virtual care platform for CKD patients, has the potential to manage CKD and reduce the likelihood of adverse outcomes such as ED visits and hospitalization. The proposed trial will rigorously test whether this platform deployed in realistic clinical settings can improve important patient outcomes.

## Strengths

Our study has many strengths. We are addressing an important impactful problem for patients with advanced CKD in a rigorous scientific design (RCT). This design will minimize bias and strengthen the internal validity of the results. Inclusion of multiple centers with diverse patient populations will enhance the external validity of our study. In this regard, we have included both academic, tertiary care referral centers, as well as community practices in order to be more broadly representative of clinical practice settings in Canada. The trial will be powered to detect a meaningful change in a clinically meaningful outcome for patients. Our intervention has been designed specifically for patients with CKD. Our previous published work has taught us that this disease-specific focus in the context of a telemonitoring intervention is important.

## Limitations

Our trial has some limitations. Patients with CKD tend to be older, of lower socioeconomic status, and often have limited health and digital literacy skills.^
1
^,^21
[Bibr bibr22-20543581251359736]-23^ This could influence their engagement in this study. Previous data also showed that many individuals from remote areas encounter difficulties in both accessing and utilizing broadband Internet services.^
24
^ The barriers are higher in Indigenous communities that have higher rates of CKD compared to the general population.^
25
^ The restricted Internet access within this population could impact their involvement in this study.

## Conclusion

In summary, optimized virtual care models could improve care of patients with complex chronic disease such as CKD patients. The VIEWER is a user-friendly, highly feasible platform designed by our multidisciplinary team to enhance virtual clinical care for CKD patients and reduce adverse, burdensome, and costly outcomes such as ED visits, hospitalizations, and acute inpatient dialysis initiation. Our findings could potentially influence CKD management in Canada and internationally.
